### Sample size

2.4

The sample size was estimated using an Analysis of Covariance (ANCOVA) for the primary outcome: the change in MADRS score from baseline (W0) to Week 6 (W6). Based on prior exploratory research (21) and the conversion formula by Leucht et al. (22), the pre-specified between-group difference (Δ) was set at approximately 2.4 points. An assumed common standard deviation (SD) of approximately 6.0 points for MADRS change scores was adopted, which is consistent with reported variability in previous studies of depression in Parkinson’s disease. This corresponds to a standardized effect size (Cohen’s d) of approximately 0.40. Statistical parameters were set at α = 0.05 (two-tailed) and a power of 1-β = 80%. The calculation, performed using G*Power 3.1 (23), indicated that 35 completers per group are required. To account for a potential 20% dropout rate, we plan to recruit 44 participants per group, resulting in a total sample size of 88. Although the primary analysis will use a mixed-effects model for repeated measures (MMRM), the sample size was estimated using an ANCOVA framework as a conservative approximation for the baseline-adjusted between-group comparison at Week 6.

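### The printed planning inputs need about 100 completers per group, not 35; on those inputs 35 per group gives about 38% power, not 80%

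*Protocol article*

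**What the plan says.** All the planning figures are in Section 2.4 (Sample size) of the protocol article.

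- **Method:** "The sample size was estimated using an Analysis of Covariance (ANCOVA) for the primary outcome", the change in MADRS from baseline to Week 6.
- **Effect:** "the pre-specified between-group difference (Δ) was set at approximately 2.4 points".
- **Variability:** "An assumed common standard deviation (SD) of approximately 6.0 points for MADRS change scores was adopted".
- **Standardized effect:** "This corresponds to a standardized effect size (Cohen’s d) of approximately 0.40".
- **Error rates:** two-tailed α = 0.05 and 80% power.
- **Result:** G*Power 3.1 "indicated that 35 completers per group are required". This is raised to 44 per group (88 in total) for 20% dropout.

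The section adds that the analysis itself will be an MMRM and that ANCOVA was used "as a conservative approximation for the baseline-adjusted between-group comparison at Week 6". It gives no pre-post correlation, R² or other variance reduction. Section 2.8.1 puts the MCID at about 2 points.

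**The concern.** A two-group comparison at d = 0.40 with 80% power is well known to need roughly 100 per group, so 35 stands out at once. The article prints both its inputs and its result, and the two disagree. This is therefore not a detail left to a fuller protocol or analysis plan: a later document could supply a missing input, but it cannot make the printed statement correct as it stands.

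The calculation is the only justification given for enrolling 88 patients, and it concerns the primary endpoint. The planned difference of 2.4 lies just above the stated MCID. If true power at that difference is far below 80%, a non-significant Week 6 result says little about whether a worthwhile benefit exists, and a reader relying on the stated 80% would not know it. Section 3 (Discussion) acknowledges a modest sample size, but only as a limit on generalizability.

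**Working it through.** **Inputs** (Section 2.4, with 1:1 allocation from Section 2.5): Δ = 2.4; SD of change = 6.0; two-sided α = 0.05; power 80%; 35 completers per group; 20% dropout.

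**1. Steps that reproduce.** d = 2.4 / 6.0 = 0.40. Dropout: 35 / (1 − 0.20) = 43.75, rounded up to 44 per group, 88 in total. The error therefore lies between d = 0.40 and 35.

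**2. Required sample size.** Normal approximation: n = 2(1.960 + 0.842)² / 0.40² = 98.1, so 99 per group. Exact noncentral t: 99.08, so 100 per group. ANCOVA noncentral F with f = d/2 = 0.20 and one or four covariates: 199 in total. With 20% dropout, 100 / 0.80 = 125 per group.

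**3. Power of the planned sizes, no variance reduction (exact t).**
- 35 per group: 37.8%.
- 44 per group, all analysed: 45.8%.

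**4. What 35 per group can detect.** 80% power needs d = 0.679. That is 0.679 × 6.0 = 4.1 points at SD 6.0, or a residual SD of 2.4 / 0.679 = 3.5 at a 2.4-point difference.

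**5. Possible slips.** None of these gives 35 per group:
- one-sided α: 78 per group;
- paired t: 52 in total;
- d entered as f (f = 0.40): 52 in total, 26 per group;
- repeated-measures F tests with 2 or 5 time points, f = 0.20 or 0.40 and an assumed correlation of 0.5: totals from 10 to 150, none equal to 70.

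Rounding does not explain it either: d = 0.45 needs 79 per group and d = 0.50 needs 64.

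**6. Baseline adjustment (assumed values, since none is stated).** Let σ₀ and σ₁ be the baseline and Week 6 SDs and ρ their correlation. The ANCOVA residual variance as a fraction of the change-score variance is

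σ₁²(1 − ρ²) / (σ₀² + σ₁² − 2ρσ₀σ₁).

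If σ₀ = σ₁, this reduces to (1 + ρ)/2:

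| ρ | Fraction | Residual SD | n per group for 80% | Power at 35 | Power at 44 |
|---|---|---|---|---|---|
| 0 | 0.50 | 4.24 | 51 | 65% | 75% |
| 0.3 | 0.65 | 4.84 | 65 | 53% | 63% |
| 0.5 | 0.75 | 5.20 | 75 | 48% | 57% |
| 0.7 | 0.85 | 5.53 | 85 | 43% | 52% |

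**7. What would make 35 right.** The fraction would have to be (0.40 / 0.679)² = 0.35. Two routes lead there:
- *Unequal SDs.* With σ₁/σ₀ = 0.6 and ρ = 0.3: 0.36 × 0.91 / (1 + 0.36 − 0.36) = 0.328, about 34 per group, 82% power at 35. At σ₁/σ₀ = 0.8 the fraction is 0.502, about 51 per group, 64% power.
- *6.0 as a raw-score SD.* With ρ = 0.8 the residual SD is 6.0 × √(1 − 0.64) = 3.6, which needs 37 per group and gives 78.5% power at 35.

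**The case against.** The best defence is that 38% is not the power of the planned analysis. Section 2.10 adjusts for baseline MADRS, the stratification factors and expectancy, and any gain from these raises power. That is right, so 38% and 46% must be labelled as the values on the printed inputs with no variance reduction. Nor is any single adjusted range the only one possible: indexed by the baseline-change correlation at 0.3 to 0.7, instead of the pre-post correlation, power at 35 per group is 41% to 64%.

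A reader might go further and infer that baseline adjustment could never close the gap. The documents do not support that. The floor of 51 per group at ρ = 0 assumes equal SDs, and a Week 6 SD about 0.6 of the baseline SD would bring the requirement to about 34. The entry range of MADRS 7–34 restricts baseline spread and makes such a ratio less likely, but does not exclude it. A reader might also infer that the trial will more often miss the planned effect than find it. The adjusted values of 52% to 63% at 44 per group contradict that as a general statement.

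On the word conservative, Section 2.4 applies it to ANCOVA relative to the MMRM, not to the number 35. The wrong sample size does not by itself refute that comparison.

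Finally, nothing in the article plans to read a null result as no benefit, and Section 2.8.1 already says that results will be interpreted against the MCID. The risk of misreading comes from the incorrect power figure, not from a stated rule.

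None of this supplies an input that yields 35.

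**Conclusion.** The sample-size statement is wrong as written. The printed inputs need 100 completers per group, almost three times the 35 reported. On them, power is about 38% at 35 per group and 46% at 44, and this part needs no assumption beyond the printed figures. With equal SDs and a pre-post correlation of 0.3 to 0.7, baseline adjustment still leaves power at 53% to 43% (35 per group) or 63% to 52% (44 per group).

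The number 35 could be rescued only by a residual variance of about 35% of the change-score variance, or by 6.0 being a raw-score SD with a correlation of about 0.8. The article states neither, and the second contradicts its description of the SD. The finding is that 35 does not follow from what is printed, not that no set of inputs could justify it.

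**What to change.** In Section 2.4:

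1. State what was entered in G*Power: effect size f, any correlation or R², and whether 6.0 is a raw-score or a change-score SD.
2. If a documented variance reduction supports 35, print it with its source. If not, replace the 80% claim with the power that 35 and 44 per group deliver (about 38% and 46% on the printed inputs), show adjusted values only beside the assumptions behind them, and give the detectable difference of about 4.1 points at 35 per group.
3. Keep any remark on ANCOVA versus MMRM separate from the number, so that 35 per group is not presented as conservative.
4. State that the Week 6 result will be read from its 95% CI against the MCID of about 2 points, so that a non-significant result is not taken as absence of benefit.

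The cost is rewording and a less favourable stated power. No extra enrolment is required. Keeping 80% power on the printed inputs would instead mean about 125 per group after 20% dropout, which is a separate decision for the sponsor.

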### Randomization and allocation concealment

2.5

This study will use a centralized randomization system to ensure unpredictability and allocation concealment. Eligible participants will be randomized in a 1:1 ratio to either the acupuncture group or the waitlist control group. Stratified block randomization will be employed to ensure baseline balance for key prognostic factors. The stratification factors are: (1) baseline depression severity (MADRS ≤ 19 vs. >19) and (2) stable antidepressant medication use (Yes vs. No). The randomization sequence will be automatically generated by the central system. After a participant provides informed consent and completes the baseline assessment, the investigator will retrieve the group assignment from the system and record it on the case report form (CRF).

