### Blinding

2.6

Given the nature of the acupuncture intervention, it is not feasible to blind participants or acupuncturists. Therefore, to minimize bias, this study will employ a single-blind (assessor-blind) design, implementing the following measures:

Blinding of Key Personnel: All outcome assessors, data managers, and statisticians will remain blinded to treatment assignment until the database is locked.Separation of Roles: Acupuncturists will not participate in outcome assessment or data management. Conversely, outcome assessors will not be involved in the intervention process to prevent unintentional bias. Acupuncturists will receive standardized training before the trial and adhere to a communication protocol with participants to avoid disclosing any group-related information.Emergency Unblinding Procedure: In the event of a serious adverse event (SAE) or other urgent medical situations where knowledge of group assignment is necessary for participant management, the principal investigator must request approval from the ethics committee. Upon approval, an independent, unblinded data administrator will perform the unblinding. The reason, time, and personnel involved in the unblinding will be fully documented. The unblinded participant will discontinue the study intervention but will continue safety follow-up. Data from unblinded participants will remain in the primary analysis according to the intention-to-treat principle.To further minimize expectancy-related bias, participants’ baseline expectations regarding acupuncture will be assessed using the Acupuncture Expectancy Scale. Expectancy scores will be included as covariates in the primary statistical analysis.To formally evaluate the success of assessor blinding, after completion of the primary endpoint assessment at Week 6 (and, if applicable, at Week 24), blinded outcome assessors will be asked to guess each participant’s treatment allocation (acupuncture or waitlist control) and to indicate their confidence level. Blinding success will be evaluated descriptively by calculating (1) the proportion of correct guesses relative to chance level and (2) Bang’s Blinding Index (BBI) with corresponding 95% confidence intervals. A BBI value close to zero will be interpreted as indicating successful blinding. These analyses are intended to assess the adequacy of blinding procedures rather than to test treatment effects.

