#### Waitlist control group

2.7.2

Participants in the waitlist control group will continue their stable, standard medication regimen for the 6-week study period. They will not receive acupuncture or any other study-specific interventions during this time. For ethical reasons, participants in the control group will be offered compensatory acupuncture treatment (using the same protocol as the acupuncture group) after the 6-week intervention period concludes.

To ensure comparability, all participants in both groups must maintain a stable antiparkinsonian medication regimen throughout the study. If any dose adjustments are necessary, they will be assessed by the investigator, documented in the CRF, and converted to the levodopa equivalent dose (LED) (26). No new systemic interventions that could potentially affect depressive symptoms will be permitted during the study. All changes in concomitant medications will be fully documented.

The use and dosage of antidepressant medications will be kept stable whenever possible throughout the 6-week controlled period. “Stable” is defined as no initiation, discontinuation, or dose change within 4 weeks prior to enrollment. During the trial, clinically indicated adjustments will be permitted for safety reasons or symptom worsening. All changes (type, dose, timing, and reason) will be documented and accounted for in the ITT analysis, with sensitivity analyses performed to assess robustness.

To monitor potential contamination during the waitlist period, at each assessment visit participants will be asked using a standardized checklist whether they have received any acupuncture or other non-study interventions for mood or motor symptoms (including acupuncture, electroacupuncture, moxibustion, rTMS, or psychotherapy) since the last visit. Any such use will be recorded as a protocol deviation (type, frequency, timing, and provider) and considered in the per-protocol and sensitivity analyses.

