### Data collection and management

2.11

Research data will be collected using a standardized Case Report Form (CRF) covering demographic information, disease history, scale scores, laboratory results, and adverse events. All scales will be administered by trained investigators in a quiet, private environment. Questionnaires will be collected on-site and immediately checked for completeness.

Data will be double-entered by two research assistants into a password-protected electronic data capture (EDC) system with built-in logic validation. Any inconsistencies will be resolved through third-party verification. The principal investigator will conduct periodic spot checks, and an independent clinical research associate (CRA) will perform scheduled quality audits. All modifications will be recorded in the audit trail.

To protect confidentiality, participants will be identified only by unique codes, and statisticians will remain blinded until the database is locked. Data will be encrypted and stored on restricted servers, while paper CRFs will be kept in locked cabinets for a minimum of 5 years. Following publication, de-identified participant-level data and statistical code will be made available upon reasonable request, in accordance with the Declaration of Helsinki and relevant regulations (38). The full protocol is available upon request. Trial results will be disseminated through peer-reviewed publications and conference presentations.

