### Quality control and monitoring

2.12

All investigators will receive standardized training prior to the trial to ensure protocol adherence, standardized data collection, and consistent reporting of adverse events. Acupuncture procedures will be performed exclusively by licensed acupuncturists following strict standard operating procedures (SOPs). Adherence will be documented through attendance logs. Good adherence is defined as the completion of ≥80% of scheduled treatment sessions. All protocol deviations or discontinuations will be recorded and addressed in the final analysis.

An independent clinical research associate (CRA), operating independently of the research team, will periodically review study progress, safety, and data quality. Core outcome measures (MADRS, MDS-UPDRS III) will be assessed by trained, blinded evaluators. Efforts will be made to standardize assessment time points and, where possible, maintain the same evaluator for each participant’s follow-up visits to minimize bias.

As a single-center study, daily management is coordinated directly by the principal investigator without a separate steering committee. Given the low-risk nature of acupuncture, a formal Data Monitoring Committee (DMC) is not established, and no interim analysis is planned.

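### Recording the group assignment on the CRF that also carries the outcome data conflicts with the stated blinding of data managers and leaves assessor blinding unprotected

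*Protocol article*

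**What the plan says.** **Allocation (section 2.5, Randomization and allocation concealment).** Once consent and the baseline assessment are complete, "the investigator will retrieve the group assignment from the system and record it on the case report form (CRF").

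**Blinding (section 2.6).** "All outcome assessors, data managers, and statisticians will remain blinded to treatment assignment until the database is locked". The same section keeps assessors out of the intervention process and binds acupuncturists to a communication protocol. Emergency unblinding goes through ethics committee approval and an independent unblinded data administrator. Assessors guess the allocation at Week 6, and the guesses are summarized with Bang's Blinding Index.

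**Data handling (section 2.11).** "Research data will be collected using a standardized Case Report Form (CRF) covering demographic information, disease history, scale scores, laboratory results, and adverse events". Then: "Data will be double-entered by two research assistants into a password-protected electronic data capture (EDC) system". On who runs the scales: "All scales will be administered by trained investigators in a quiet, private environment".

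**Quality control (section 2.12).** "Core outcome measures (MADRS, MDS-UPDRS III) will be assessed by trained, blinded evaluators". The same evaluator is kept for a participant's visits where possible.

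**Contamination check (section 2.7.2, Waitlist control group).** The stated purpose is to monitor contamination during the waitlist period, and "at each assessment visit participants will be asked using a standardized checklist whether they have received any acupuncture". The sentence goes on to other non-study interventions for mood or motor symptoms. Any use is to be recorded as a protocol deviation.

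**The concern.** Participants and acupuncturists know the treatment, and there is no sham procedure. The primary outcome is the change in MADRS at Week 6, which is scored by a rater. Blinding of the people who rate and handle the data is therefore the main protection the design has against differential scoring. The planned between-group difference is about 2.4 points (section 2.4), so there is little room for a rater effect.

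Against that background, the text sends the allocation to the document that carries the outcome scores. It also has acupuncture asked about at the visits where those scores are obtained. The Bang index can show afterwards that blinding failed, but it cannot undo a rating made with knowledge of the arm.

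**Working it through.** No arithmetic applies. The check sets the sections side by side, role by role.

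**1. Data managers.** Section 2.5 places the assignment on the CRF. Section 2.11 describes one standardized CRF that includes the scale scores, with its data entered twice into the EDC and discrepancies settled by third-party verification. All of this must happen before lock. Section 2.6 says data managers do not know the assignment until lock. No sentence provides a separate, sealed or access-restricted allocation page, or a hidden field in the EDC. If the three sections are followed literally, those who enter and check the CRF see the arm. This assumes that data entry and checking count as data management in the sense of section 2.6, which is the natural reading.

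**2. The emergency procedure.** Section 2.6 treats the assignment as sealed: the principal investigator must request ethics approval, and an unblinded administrator then reveals it. Section 2.11 has the principal investigator make spot checks of the data. If the arm is already written on the CRF, the sealed procedure has little left to protect. Sections 2.5 and 2.6 need to be reconciled on this point too.

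**3. Outcome assessors.** In section 2.5 the investigator records the allocation. In section 2.11 investigators administer all the scales. In section 2.12 blinded evaluators rate MADRS and MDS-UPDRS III. Section 2.12 settles that the raters are meant to be blinded. Nothing says, however, that they are kept away from the CRF entry or that they are different people from the investigators of section 2.5. The separation of roles in section 2.6 concerns taking part in the intervention, not access to forms. This is an unguarded route, not a demonstrated breach.

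**4. The checklist, visit by visit.**
- At baseline no trial treatment has been given, so the answer reveals nothing about the arm.
- At Week 6 the acupuncture group has had its course and the controls have had none. If the question is taken to include trial acupuncture, a truthful answer identifies the arm at the primary-endpoint visit.
- After Week 6 controls are offered the same acupuncture, so a positive answer separates the groups less well. A disclosure at Week 6 could still carry forward where the same evaluator is kept.

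The text does not say who asks the question, or whether it comes before or after the rating.

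**5. Adverse events.** Table 1 schedules them at Week 6. Section 2.9 lists needling reactions and requires a judgement of their relationship to the intervention. It assigns this to the research team, not to assessors. That is a reason to keep those pages out of the raters' view, but it does not show that raters complete them.

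**6. Statisticians.** Sections 2.6 and 2.11 both say they stay blinded until lock. Nothing gives them the CRF or arm-labelled data before then, so no conflict is found.

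**The case against.** The strongest reply is that this is a condensed article. Section 2.11 says the full protocol is available on request, and form layout, EDC permissions and the order of tasks at a visit commonly stand there. A CRF is usually a set of forms, and the allocation page need not travel with the rating pages. The trial already names an unblinded data administrator, so it distinguishes blinded from unblinded data roles. Section 2.12 expressly calls for blinded evaluators.

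On the checklist, the mention of other non-study interventions, the contamination purpose, the placement under the waitlist heading and the protocol-deviation rule all suggest that only acupuncture outside the trial is meant. Assigned acupuncture cannot sensibly be a deviation. Finally, data managers do not rate MADRS, so their knowing the arm does not itself bias the primary outcome.

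Much of this stands. It rules out the stronger inference a reader might draw, that the blinding of assessors, data managers and statisticians is all defeated. No section says that an assessor sees the allocation entry or asks the checklist, and none gives statisticians arm-labelled data before lock.

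It does not remove the conflict itself. The article does more than stay silent on form access: it states affirmatively that the assignment goes on the CRF, and that statement works against its own blinding claim. The narrower reading of the checklist is plausible but not fixed by the wording, which asks participants in general about any acupuncture.

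**Conclusion.** The point holds in a limited form. Sections 2.5, 2.6 and 2.11 conflict as written over the blinding of data managers, and they leave assessor blinding without a stated barrier at the CRF. The checklist in section 2.7.2 is a second possible route of disclosure. It matters mainly at Week 6, and only if the question is taken to cover trial acupuncture and the rater asks it or learns the answer before rating.

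The size of any resulting bias in MADRS cannot be estimated: the document gives no figure for how far ratings might shift if raters knew the arm. The conclusion rests on reading the CRF as the single standardized form that section 2.11 describes. Access rules in the full protocol could resolve the conflict in practice, but the article's text would still need correcting. The correction is worth making because it is nearly free and protects the main safeguard of a rater-scored primary outcome in a trial whose participants know their treatment.

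**What to change.** - In section 2.5, delete the instruction to write the assignment on the CRF. State that it is held only in the central randomization system, or in a restricted log open to unblinded staff.
- In section 2.7.2, limit the checklist wording to non-study acupuncture and other non-study interventions.
- Have existing unblinded staff complete the checklist, together with session attendance and needling-related adverse event pages, on a form with restricted access. This should follow submission of the MADRS and MDS-UPDRS III ratings at that visit.
- Instruct participants not to mention their treatment to assessors.
- In section 2.11, align the description of who administers the scales with the blinded evaluators of section 2.12.

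The cost is a minor split of the CRF and EDC forms, wording on the order of tasks at visits, and some extra handling by unblinded staff. No participants, visits or measurements are added.
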